### Inclusion Criteria and Exclusion Criteria

Inclusion criteria are burn patients of legal adult age admitted to the ICU of the University Hospital Fundación Santa Fe de Bogotá; and an estimated hospitalization of >7 days. Exclusion criteria are patients with known psychiatric disorders; patients with cognitive disabilities; and sedated and/or mechanically ventilated patients.

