### Intervention

Participants in the intervention group will take part in a Music Assisted Relaxation (MAR) protocol. MAR is a music therapy technique that includes listening to live music based on the principles of entrainment (42, 43), combined with deep diaphragmatic breathing and guided relaxation and imagery. In the first step, the procedure of the intervention is explained to the patient, and he/she is asked to close the eyes or focus on a fixed point on the ceiling or wall. This is followed by a verbal introduction focusing on body and respiratory awareness. A mental image is then introduced, for example: sitting on a beach watching the waves of the sea; being on top of a mountain contemplating the horizon; imagining a personalized safe and comfortable place; among others. The patient is asked to breathe with the music while concentrating on the imagery and sounds. While the improvised music can change according to each patient and situation, it usually consists of a slow tempo, simple harmonic structures, free-flowing melodies, avoiding large intervals or abrupt changes in tonalities. The musical instruments used are a classical guitar with nylon strings (Yamaha C-40), an ocean drum (a drum with a double skin over which small metal pallets role imitating the sound of waves) and a Samafon (an instrument consisting of aluminum/copper tubes of different sizes that are stuck with a soft mallet producing long-lasting single or combined tones). Once the music stops, the patient is asked to become aware and the experience during the session is verbally elaborated. Each intervention will last between 30 and 40 min and will be delivered three times per week from the day of study entry up to a maximum of 2 weeks or six interventions in total. The time frame and frequency of the interventions has been chosen to stay close to daily clinical practice, in which the music therapy team of the FSFB usually sees patients 2-3 times per week. This has been a therapy frequency working well in terms of being able to offer a process-oriented approach, but not to overstrain patients due to their numerous commitments with other therapies and medical procedures. With respect to the time frame, burn patients stay in the ICU of the FSFB an average of 13,9 days, with 42% staying up to 1 week, 19% up to 2 weeks, and 38% more than 2 weeks. However, depending on the medical condition, it might take a couple of days or more from admission onwards until the patient is medically stable enough to start therapy. Thus, an intervention period of 2 weeks was chosen to capture most of the population. The musical instruments are disinfected and cleaned according to a protocol that has been published elsewhere (44).

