### Secondary Outcome Measures

The Colombian version of the Hospital Anxiety and Depression Scale (HADS) (45) will be applied to measure anxiety and depression levels of the participants. The HADS consists of a 7-item anxiety subscale and a 7-item depression subscale rated on a four-point Likert scale. The higher the total points on each scale, the greater the risk of a depressive or anxiety disorder, with a maximum score of 21 for each subscale. The HADS scale will be applied at baseline, after the third, and after the last intervention. Period of data collection: maximum 2 weeks from the point of study entry.Vital signs (heart rate, respiratory rate, oxygen saturation, blood pressure) will be measured via hospital monitors before the intervention, after the intervention, and at 3 h post-intervention. Period of data collection: maximum 2 weeks from the point of study entry.The use of pain medication refers to the frequency and dose of additional analgesic medications requested by the patient during the study period (complementary or rescue doses). The total amount of dosage and frequency will be calculated by summing up individual records. Period of data collection: maximum 2 weeks from the point of study entry.

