
While it is known that music itself can release neurotransmitters and hormones related to pain and stress relief (66), the trauma that many burn patients experience and the inherent link between pain and mental health requires the presence of credentialed professionals, such as music therapists. Profound relaxation can help in self-regulation but may sometimes evoke undesired emotions or thoughts. Stressing the importance of the therapeutic relationship applies also for this study, and time for verbal processing after the MAR will be used to elaborate the experiences during the intervention. While the length of the ICU stay for burn patients can fluctuate, we tried to offer a process-oriented protocol with a maximum of six interventions over the course of 2 weeks. This may not seem a lot, but to our knowledge, all other RCTs on music or music therapy interventions used single interventions or interventions over a few consecutive days) (30, 31).

Another new feature of this study is the focus on background pain instead of procedural pain. While background pain is usually lower in intensity, it is of longer duration and may thus alter pain memory in the long-term (6). This is important, since pain chronification may increase the already higher risks of burn patients in developing mental health impairments, such as acute stress disorder (ASD), post-traumatic stress disorder (PTSD), elevated stress levels, depression, and insomnia (6, 67). Especially in times of an ongoing opioid crisis, complementary treatments to pharmacological strategies for pain management in burn patients are needed not only for procedural pain, but also for background pain (68). In a previous meta-analysis of music interventions and pain in different medical settings, Lee (28) found a statistically significant reduction in opioid intake. However, in the three RCTs found with adult burn however, this result has not been replicated (33, 69, 70). In this study protocol we will try to evaluate total opioid intake during the intervention period, specifically in relation to rescue doses requested by the patients.

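### Rescue analgesic use is a raw total over an observation period that is capped but not fixed, so it depends partly on days observed and loses precision

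*Protocol article*

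**What the plan says.** Secondary Outcome Measures defines the medication outcome as "the frequency and dose of additional analgesic medications requested by the patient during the study period (complementary or rescue doses". It then gives the aggregation rule: "The total amount of dosage and frequency will be calculated by summing up individual records". The window is an upper limit only: "Period of data collection: maximum 2 weeks from the point of study entry".

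Data Management and Statistical Analysis lists use of analgesics among the secondary outcomes to be compared by ANOVA or the Mann-Whitney test. It mentions no division by days observed and no exposure term.

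The Intervention section reports a mean ICU stay of 13.9 days and shows how widely stays vary around it: "with 42% staying up to 1 week, 19% up to 2 weeks, and 38% more than 2 weeks". It adds that "it might take a couple of days or more from admission onwards until the patient is medically stable enough to start therapy". Eligibility requires "an estimated hospitalization of >7 days", which is a forecast and concerns the hospital stay rather than the ICU stay.

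The Discussion describes the same outcome in other words: "we will try to evaluate total opioid intake during the intervention period, specifically in relation to rescue doses requested by the patients".

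**The concern.** A sum of doses is the product of two things: how much a patient asks for per day, and for how many days requests are recorded. Only the first is what music-assisted relaxation is meant to change. When the second differs between patients, it adds variation unrelated to the treatment question, and neither planned test removes it.

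Medication use is a named secondary objective and part of the study hypothesis. With about 40 patients per arm there is little precision to spare. A real reduction in daily use could be missed, and a chance difference in observed time between arms would carry straight into the totals.

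**Working it through.** **Inputs from the article.** ICU stay split 42/19/38% and mean 13.9 days (Intervention); a start delay of a couple of days or more (Intervention); a cap of 14 days (Secondary Outcome Measures); 81 patients at 1:1, so about 40 per arm.

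**Inputs assumed, because the article gives none.** Stays uniform within strata at 2–7, 7–14 and 14–34 days; start delay 0 to 4 days; mean daily rate μ = 2 rescue doses (1 also tried); between-patient CV of the daily rate c from 0 to 1.0; doses Poisson given each patient's rate.

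**Check on the stay assumption.** The article gives no figure for the medication outcome, but the assumed strata can be set against its mean stay. The three shares add to 99, so the mean is (42 × 4.5 + 19 × 10.5 + 38 × 24)/99 = 1300.5/99 = 13.1 days, close to the stated 13.9.

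**Step 1: share of variance due to days observed.** For days observed T and total Y:

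Var(Y) = μ²·Var(T) + c²·μ²·E(T²) + μ·E(T)

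The first term is the part due to T. Simulated T with a 2-day delay:

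- All ICU stays: mean 8.74, SD 4.98, so Var(T) = 24.8 and E(T²) = 76.4 + 24.8 = 101.2. At μ = 2 and c = 0.5 the terms are 99.2 + 101.2 + 17.5 = 217.9, and the share is 99.2/217.9 = 46%. At c = 1.0 it is 99.2/(99.2 + 404.8 + 17.5) = 19%.
- Only stays above 7 days: mean 12.10, SD 2.81, so Var(T) = 7.9 and E(T²) = 146.4 + 7.9 = 154.3. At c = 0.5 the share is 31.6/(31.6 + 154.3 + 24.2) = 15%. At c = 1.0 it is 31.6/(31.6 + 617.2 + 24.2) = 5%.

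**Step 2: price in patients.** For the same relative difference, the sample size ratio (total versus per-day rate) is about (CV of total / CV of rate)². With the 2-day delay and μ = 2:

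| Stays entering | c | CV total | CV rate | n ratio |
|---|---|---|---|---|
| All | 0.5 | 0.84 | 0.59 | 2.02 |
| All | 1.0 | 1.30 | 1.05 | 1.54 |
| Above 7 days | 0.5 | 0.60 | 0.54 | 1.22 |
| Above 7 days | 1.0 | 1.07 | 1.02 | 1.10 |

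(Ratios come from unrounded CVs.)

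**Step 3: power.** Simulation with 40 per arm, μ = 2, a true 40% lower daily rate and the Mann-Whitney test. At c = 0.7:

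| Stays entering | Start delay | Sum | Per day | Loss (points) |
|---|---|---|---|---|
| All | 0 days | 58% | 76% | 18 |
| All | 3 days | 34% | 69% | 35 |
| Above 7 days | 0 days | 78% | 81% | 3 |
| Above 7 days | 3 days | 71% | 77% | 6 |

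Over c = 0.5 to 1.0 and delays of 0 or 3 days, power is 25–67% (sum) against 41–94% (per day) with all stays, a loss of about 10 to 47 points. With stays above 7 days only, it is 42–94% against 45–97%, a loss of about 0 to 8 points. The largest loss is in the setting with all stays, a 3-day delay and c = 0.5.

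**Step 4: type I error and unequal follow-up.** With identical daily use and the same distribution of days in both arms, the test rejects in 5.1% of trials for sums and for per-day rates alike. If mean days differ between arms, the ratio of totals is the rate ratio times the days ratio. With no effect and 20% fewer days it is 1.00 × 0.80 = 0.80. With a true 25% fall it is 0.75 × 1.20 = 0.90 or 0.75 × 0.80 = 0.60.

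**The case against.** The strongest reply is that the size of the problem rests on inputs the article does not fix. The 42/19/38 split describes burn patients in this ICU generally, not trial participants, and the eligibility rule screens out many short stays. Nor does the article say that medication recording stops at ICU discharge. If records ran for the full 2 weeks in nearly everyone, the total and the per-day rate would give almost the same answer. This stands. It is why the loss must be given as a range whose lower end is near zero. It does not remove the point: the eligibility rule is an estimate about hospital stay, the window is only a maximum, and the sum is a stated rule rather than a detail left to the SAP.

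A reader might infer four stronger things, which the article does not support.

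- *That the outcome mainly measures length of stay.* At between-patient CVs of 0.5 to 1.0, days observed exceeded half the variance in only one of twelve settings examined (56%, with all stays, a 3-day delay and CV 0.5). They dominate only when daily use is much alike across patients.
- *That the comparison is biased.* Allocation is randomized 1:1, so observed time is balanced in expectation and type I error holds. A false signal appears only when a difference in observed days is put in by hand, and nothing in the article predicts one.
- *That milligrams of different drugs are added together.* Summing individual records is compatible with totals per drug or in equivalents, and the frequency component needs no common unit. Conversion is ordinary SAP content.
- *That the outcome definition and the Discussion contradict each other.* Opioids are a subset of analgesics, and both places refer to rescue doses requested by the patient. The wording is loose and worth aligning, no more.

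**Conclusion.** The point holds as a matter of precision on a secondary outcome. The article fixes a raw total over unequal observation times and compares it without exposure time, so part of its variation comes from days observed.

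The power loss is about 10 to 47 points if all ICU stays enter and about 0 to 8 points if only stays above 7 days enter. The true figure depends on who is enrolled and when recording ends. Both ranges rest on assumed values: 2 doses a day, between-patient CV 0.5 to 1.0, a start delay of 0 or 3 days, 40 per arm and a 40% lower daily rate. With equal follow-up the test remains valid. Unequal follow-up, if it occurred, would move the total in proportion, but that is a vulnerability and not an expected bias. This is a cheap improvement worth making, not a threat to the trial's primary conclusion.

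**What to change.** In Secondary Outcome Measures, define the outcome as rescue doses, and dose amount, per day observed. A count model with log observed days as offset is an equally acceptable form for the number of doses. State one rule for when medication recording ends and apply it identically in both arms. Use the same drug class in Secondary Outcome Measures and in the Discussion. Raw totals can still be reported descriptively, and the choice of a common unit for dose amounts can be left to the SAP.

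The cost is slight. The individual dose records already have to be kept for the planned sum, so what is added is each patient's number of days observed and a little analysis work. The one drawback is that simple per-day rates are noisier for patients observed only briefly. The offset model lessens this because such patients carry less information in it.

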### Other Outcome Measures

In about 20% of the patients in the intervention group (approx. eight participants), additional Electroencephalogram (EEG), Electrocardiogram (ECG) and Electromyography (EMG) recordings will be made. Since this is an exploratory feature of the study, participation in the EEG, ECG, and EMG measurements is voluntary and depends on the location of the burn wounds, the clinical stability of the patient, and is defined together with the attending physician. The sample size of 20% was chosen based on an estimation of potential participants without any head/face/neck burn injuries, in which the application of electrodes would not be feasible. As the aim of the MAR is to help patients achieve relaxation, the hypothesis for these measurements is that this will lead to (1) an increase in Alpha and Theta brain waves, both of which correspond to deep relaxation and inward-focused states of mind; (2) a reduction in muscular tone; and (3) changes in the high frequency (HF) and low frequency (LF) components and in the LF/HF ratio indicating a parasympathetic activation. All these physiological variables will be acquired simultaneously with a Micromed LTM64 (Micromed S.P.A., Italy) acquisition system, with a sampling frequency of 512 Hz. The Micromed LTM64 is of clinical quality and has the due approval of the Colombian National Institute for Drug and Food Safety (20090486-2015). For the EEG recordings, the international 10-20 scalp system setup will be used, but the final number of electrodes will depend on medical approval for each patient. From these signals, we will assess power changes in the physiological Theta (4-8 Hz), Alpha (8-12 Hz) and Beta (12-30 Hz) frequency bands, associated with brain relaxation and engagement, respectively (46, 47). The ECG will be acquired using the lead II bipolar montage with two electrodes located bilaterally in the upper chest or both arms depending on the possibilities or limitations of each patient and on his/her medical condition. From the ECG we will measure changes in heart rate and Heart Rate Variability (HRV) associated with the intervention. For this last, we will assess contributions from the sympathetic and parasympathetic branches of the autonomic nervous system through the LF and HF components from the spectral analysis of the tacogram (48). The EMG will be recorded to evaluate changes in muscular tone associated with the intervention, using a bipolar montage with two electrodes located in the chin (when possible). Muscular tone activations will be assessed through changes in amplitude of the EMG signal.

### Participant Timeline

The schedule of enrolment, interventions and assessments is shown in the following Table 1:

**Table 1 T1:** Schedule for enrolment, interventions, and assessments.

	**Study period**						
	**Enrolment**	**Allocation**	**Post-allocation**				**Closeout**
**Timepoints**	**–t_**1**_**	**t_**0**_**	**t_**1**_**	**t_**2**_**	**t_**3**_**	**etc**.	**t_**x**_**
**Enrolment**							
Eligibility screen	**x**						
Informed consent	**x**						
Allocation		**x**					
**Interventions**							
Intervention group			**x**	**x**	**x**	**x**	
Control group			**x**	**x**	**x**	**x**	
Assessments							
Baseline measures:	**x**						
Socio-demographic/Medical data	**x**						
VAS	**x**						
HADS							
**Outcome measures**							
VAS			**x**	**x**	**x**	**x**	**x**
HADS					**x**		**x**
Vital signs			**x**	**x**	**x**	**x**	**x**
Medication usage			**x**	**x**	**x**	**x**	**x**

### Data Management and Statistical Analysis

Data collection and storing will be done manually and later transcribed to an electronic database. The accuracy of data transcription will be checked by randomly selecting 20% of the participants for whom a double-data entry procedure will be implemented as a means for control of potential errors while transcribing the results from the paper questionnaires to the electronic database. The original questionnaires will be stored in a locked shelf inside the ICU and digital data storing and processing follows the institutional guidelines for data security, including a password protected laptop, encrypted files, and using secure methods of file transfers.

Data analysis will be performed by analysts blinded to the randomization outcomes and based on an intention-to-treat analysis (ITT) (49). Basic socio-demographic and medical data will be analyzed using descriptive statistics and compared between the two groups to detect any differences in the population. For the differences of the main outcome measure (pain) and the secondary outcome measures (anxiety and depression, vital signs, use of analgesics), ANOVA (analysis of variance), the *p*-value test, and the Mann-Whitney *U*-test will be performed. When analyzing the data, a univariate analysis will be carried out in which the frequency (absolute and relative), percentages and confidence intervals of the different qualitative variables will be established. Subsequently, the association between the different variables will be evaluated through the Chi-square χ^2^ test. Additionally, the Shapiro Wilk test will be used to determine the distribution of the quantitative variables. Once this result is obtained, we will seek to determine the mean, standard deviation, central tendency, and dispersion for the variables of normal distribution, while the median and interquartile range will be sought for those of non-normal distribution. These variables will be evaluated using the Student's *t*-test or the Mann-Whitney *U*-test according to the distribution. The results will be considered statistically significant when observing a value of *p* < 0.05 (5%). Finally, a multivariate analysis will be carried out where logistic regression will be used to determine the contribution of each of the different quantitative variables in terms of the observed results.

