### Data Collection and Outcome Measures

Basic socio-demographic and medical data will be collected from all participants, including age; gender; educational level; marital status; level of support by the patient's social system; medical diagnosis; type and location of the burns; and depth and surface % of the burns.

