### Primary Outcome Measure

Primary outcome measure is a Visual Analog Scale (VAS) of 0-10. 0 indicates a state without any pain and 10 indicates the most severe pain possible. Each number from 0 to 10 is distributed in a line 1 cm apart and the patient can mark the intensity of pain felt at the time of filling out the VAS. The VAS will be applied at baseline, and every time before, after, and at 3 h post-each intervention. Period of data collection: maximum 2 weeks from the point of study entry.

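### Baseline data are to be compared between randomised arms in order to find differences that randomisation makes chance; describe them without tests and fix the pain covariates in advance

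*Protocol article*

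**What the plan says.** Under Data Management and Statistical Analysis, the protocol article states that "Basic socio-demographic and medical data will be analyzed using descriptive statistics and compared between the two groups to detect any differences in the population". The variables are listed under Data Collection and Outcome Measures: "age; gender; educational level; marital status; level of support by the patient's social system; medical diagnosis; type and location of the burns", followed by "depth and surface % of the burns".

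The sentence on the baseline comparison names no test. The same section then assigns ANOVA and Mann-Whitney to the outcomes. For qualitative variables it says that "the association between the different variables will be evaluated through the Chi-square" test. Quantitative variables get a t-test or Mann-Whitney according to their distribution, and p < 0.05 is the single criterion for the results. It closes with a logistic regression that names no covariates.

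Randomization and Group Allocation gives individual 1:1 allocation. Pain is also recorded at study entry: "The VAS will be applied at baseline, and every time before, after, and at 3 h post-each intervention".

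**The concern.** The stated purpose of the comparison is mistaken. When patients from one source are allocated at random, the hypothesis of no population difference between the arms is true by design. A small p-value at baseline then shows only that chance produced an unusual split. A large one does not show that the arms are comparable in ways that matter for pain, because a p-value measures neither the size of an imbalance nor its link to the outcome.

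Two misreadings are at stake. A chance finding may be taken as a fault in the randomisation, or may prompt a covariate to be added once the data are known. A prognostic imbalance that falls short of significance may be ignored. The article does not say what follows from a detected difference, so nothing in it guards against either.

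**Working it through.** **Which tests could apply.** The outcomes are VAS, HADS scores, vital signs, and analgesic dose and frequency, all of them scores, measurements or counts. The qualitative variables in this trial are therefore essentially the baseline ones. That makes chi-square on baseline data the natural reading, though not an explicit one.

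**Inputs.**
- Number of variables k: 8 as the list is punctuated; 10 if burn type and location, and depth and surface %, are counted separately; 13 if baseline VAS and the two HADS subscales are added ("The HADS scale will be applied at baseline, after the third, and after the last intervention").
- Significance level: 0.05 per test, two-sided, with no adjustment stated.
- Arm sizes: the article gives no error rate for baseline comparisons; its only relevant figure is the sample size. With P1 = 0.8, P2 = 0.6 and P = 0.7, its formula gives [1.96√0.42 + 0.842√0.40]² / 0.04 = 81.25, as stated. The article uses 81 as the trial total, and 1:1 allocation gives about 40 and 41. This agrees with its remark that 20% of the intervention group is about eight patients.

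**Chance of at least one spurious p < 0.05.** For independent tests this is 1 − 0.95^k. For an assumed common correlation ρ among the test statistics it is 1 − ∫ φ(u) [Φ((1.96 − u√ρ)/√(1−ρ)) − Φ((−1.96 − u√ρ)/√(1−ρ))]^k du.

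| k | independent | ρ = 0.3 | ρ = 0.5 |
|---|---|---|---|
| 8 | 33.7% | 30.0% | 25.0% |
| 10 | 40.1% | 35.1% | 28.7% |
| 13 | 48.7% | 41.8% | 33.4% |

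A simulation with t-tests and chi-square tests at 40 and 41 patients, using assumed category shares, gave 39.7% for 10 tests and 48.7% for 13. Discreteness of the chi-square tests therefore changes little.

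**Imbalances that pass unnoticed.** The standard error of a standardised mean difference is √(1/40 + 1/41) = 0.222. The significance threshold is 1.96 × 0.222 = 0.44 SD. A hypothetical observed imbalance of 0.40 SD gives z = 0.40/0.222 = 1.80 and p = 0.072, which is non-significant.

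**What adjustment could gain.** If a baseline covariate correlates r with the pain outcome, adjusting for it multiplies the residual variance by about 1 − r². The article gives no r. For assumed values of 0.3 and 0.5 the reduction is 9% and 25%, and it does not depend on whether the arms look balanced.

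**The case against.** The strongest reply is that the sentence promises descriptive statistics and a comparison, not significance tests. The tests appear later in the section and have another plausible use, since one secondary objective is to examine medical and social factors associated with the effect of the intervention. If baseline data are only described, no false-positive figure applies. This stands in part: testing is an inference. It does not rescue the stated aim of detecting population differences, and the section offers no other between-group method.

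A reader might infer that 40 to 49% of such trials would flag a false difference. The documents do not support that as a flat statement. It needs significance testing, 10 to 13 variables and independence. The upper figure also counts VAS and HADS, which the article treats as outcome measures and not as basic socio-demographic and medical data. Burn type, depth, surface and diagnosis are likely to be correlated, which lowers the figure.

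A reader might also infer that the main result hangs on these comparisons, or that burn surface % is known to predict pain strongly. Neither is in the text. No decision, covariate or change of analysis is tied to the baseline comparison. Burn surface % is only listed as collected; Potential Limitations names the patient's medical condition among several influences on background pain.

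Finally, covariates are commonly left to a full protocol or analysis plan, and their absence from an article is not a fault. That is accepted. Covariates are proposed here because fixing them beforehand answers the legitimate worry about imbalance, which the baseline comparison cannot do.

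**Conclusion.** The point holds in a limited form. The purpose given for the baseline comparison is wrong under randomisation, and the tools at hand would serve it badly. If the listed variables are tested at p < 0.05, the chance of at least one spurious difference is about 29 to 40% for ten variables (correlation from 0.5 down to 0) and 25 to 34% for eight. It reaches 49% only with 13 independent tests. Observed imbalances up to about 0.44 SD would not be flagged, taking 81 as the total. Both results assume that significance tests are used, and the correlations are assumptions.

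The primary comparison does not depend on these tests. The harm is to the reading of the baseline table and to the discipline of covariate choice, not to the validity of the main result. Dropping the tests alone would change little; the worthwhile gain comes from settling the adjustment in advance.

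**What to change.** Replace the sentence with a statement that baseline characteristics will be presented by arm with descriptive statistics and no p-values; standardised differences are optional.

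State, before any data are seen, that the pain comparison will be adjusted whatever the observed balance. Baseline VAS comes first, as the same scale measured at entry. Burn surface % may be added on the stated assumption that it is prognostic. If a full protocol or analysis plan already names covariates, the wording should agree with it.

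The cost is more than one sentence: the plain t-test, Mann-Whitney or ANOVA comparison of pain becomes a covariate-adjusted one, such as an analysis of covariance. Both covariates are already collected, so no new data or patient contact is needed.
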